### aTBS protocol

Transcranial magnetic stimulation is delivered using the Magneuro system (Nanjing Vishee Medical Technology Co., Ltd.) equipped with a figure-of-eight coil (**Table 3**). DLPFC is localized using the Beam F3 method (online calculator available at https://clinicalresearcher.org/F3/calculate.php) (29).

**Table 3 T3:** List of TMS and EEG equipment.

Equipment category	Specific requirements	Purpose
aTBS Stimulation Device	Transcranial Magnetic Stimulator (MagVenture), equipped with a “figure-of-eight” stimulation coil (70mm in diameter), supporting parameter setting for the aTBS mode (frequency: 50Hz, inter-burst interval: 200ms)	Deliver precise sequential aTBS stimulation targeting the target brain region (left/right DLPFC)
ERP Acquisition System	64-Channel EEG Recorder (Brain Products ActiChamp), with a sampling rate of ≥1000Hz and a bandpass filter of 0.1-30Hz; Closed-Back Noise-Canceling Headphones (Sennheiser HD 280 Pro)	Record the P300 component evoked by the auditory oddball paradigm, while reducing environmental noise and electromagnetic interference
Stimulus Presentation Software	E-Prime 3.0, which supports the generation of auditory stimulus sequences (standard stimuli + target stimuli), synchronous triggering of EEG markers, and response recording	Control the parameters of the oddball paradigm to ensure that the stimulus timing is synchronized with EEG acquisition (error < 1 ms)
Auxiliary Equipment	International 10–20 System Electrode Cap, Non-Irritating Conductive Paste, Alcohol Wipes, Motor Threshold (MT) Measurement Tool, HAMD-17 Rating Scale	Reduce EEG impedance, determine aTBS stimulation intensity, and assess the severity of depressive symptoms

aTBS, accelerated Theta Burst Stimulation; DLPFC, Dorsolateral Prefrontal Cortex; ERP, event-related potential; EEG, electroencephalography.

Participants in the active group receive sequential bilateral aTBS twice daily for 10 treatment days. The interval between the two daily treatment sessions in this study is set at 3 hours This interval is based on the following considerations: (1) Safety: Drawing on experience from the SAINT protocol, a 3-hour interval provides sufficient safety redundancy (12); (2) Neurophysiological recovery: This interval allows the nervous system to recover from each stimulation session, avoiding excessive cumulative effects (30); (3) Tolerability: It reduces fatigue and discomfort, thereby improving treatment adherence. The aTBS protocol, illustrated in **Figure 2**, consists of cTBS applied to the right DLPFC followed immediately by iTBS applied to the left DLPFC. Specifically, cTBS delivers 1,800 pulses over 120 seconds, whereas iTBS consists of three trains of 600 pulses (3 minutes and 9 seconds each) separated by 10-second intervals, totaling 1,800 pulses over 570 seconds. The coil is positioned tangentially to the scalp with the handle pointing posterior–laterally at approximately 45°. Sham stimulation will be delivered by tilting the coil 90° away from the scalp, while maintaining identical stimulation targets, treatment duration, and procedural protocols to those of the active intervention. This sham stimulation protocol is widely accepted and utilized in clinical trials (31).

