**Methods and analysis:**

This study is a single-blind, randomized controlled trial. Fifty-six adults with MDD will be recruited and randomly assigned (1:1) to receive either active sequential bilateral Dorsolateral Prefrontal Cortex (DLPFC) aTBS (10 weekday sessions; 3600 pulses per session) consisting of continuous theta-burst stimulation (cTBS) applied to the right DLPFC followed by intermittent theta-burst stimulation (iTBS) applied to the left DLPFC, or sham stimulation. The primary outcomes will be response and remission rates based on the 17-item Hamilton Depression Rating Scale (HAMD-17). Secondary outcomes will include the Beck Depression Inventory-II (BDI-II), the Columbia Suicide Severity Rating Scale (C-SSRS), and electroencephalography (EEG)-derived electrophysiological markers of cognitive processing (P300). Safety and tolerability will be systematically evaluated throughout the study using the Treatment Emergent Symptom Scale (TESS) to record stimulation-related adverse events. Outcome measures will be assessed at baseline, immediately after the 10-day intervention, and at 2-week and 4-week follow-ups to evaluate the short-term sustainability of treatment effects.

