## Materials and methods

### Study design

This randomized, sham-controlled clinical trial was approved by the Ethics Committee of Wuxi Mental Health Center and prospectively registered in the Chinese Clinical Trial Registry (ChiCTR; official website: www.chictr.org.cn, Registration No.: ChiCTR2500109181). All procedures will adhere to the principles of the Declaration of Helsinki and the Guidelines for Good Clinical Practice (GCP). Reporting will follow the SPIRIT 2025 recommendations, and the completed SPIRIT checklist is available in **Supplementary Material S1**.

This trial will be conducted at Wuxi Mental Health Center between September 2025 and August 2027. The assessment and screening will be conducted by two practicing physicians from Wuxi Mental Health Center. Eligible participants will be randomly allocated (1:1) to receive either active sequential accelerated theta burst stimulation (aTBS; 3,600 pulses per session, 10 sessions total) or sham stimulation. Outcome measures will include the 17-item Hamilton Depression Rating Scale (HAMD-17) (24), Beck Depression Inventory (BDI-II) (25), Columbia Suicide Severity Rating Scale (C-SSRS) (26), Treatment Emergent Symptom Scale (TESS) (27) and event-related potential P300. All assessments will be administered at baseline (T0), immediately after the final stimulation session (T1), and at 2-week (T2) and 4-week (T3) follow-ups. A detailed flow diagram of the trial is shown in **Figure 1**, and the trial schedule is presented in **Table 1**.

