## Discussion

This study addresses the urgent clinical need for rapid and safe interventions targeting suicidal ideation in adults with MDD. Sequential bilateral aTBS integrates inhibitory and excitatory stimulation within a condensed treatment schedule, offering a potential balance between therapeutic efficiency and tolerability. To our knowledge, this represents the first randomized controlled trial specifically designed to systematically evaluate the efficacy and safety of sequential aTBS in adults presenting with suicidal ideation.

This trial has several notable strengths. First, as the first randomized, single-blind, sham-controlled study specifically designed to evaluate sequential accelerated theta-burst stimulation in adults with major depressive disorder accompanied by suicidal ideation, this work directly addresses a critical evidence gap in the field of neuromodulation. Second, the protocol integrates a bilateral sequential stimulation approach—right-cTBS followed by left-iTBS—that is theoretically grounded in contemporary models of interhemispheric imbalance and network dysfunction in depression (41, 42). This design allows simultaneous engagement of inhibitory and excitatory prefrontal pathways within a single session, potentially enhancing the efficiency of network-level modulation relative to single-target TBS paradigms. Third, by employing an accelerated schedule (10 sessions across 10 weekdays), the study evaluates a clinically pragmatic, time-efficient treatment model that may be particularly valuable for patients presenting with elevated suicide risk who require rapid intervention. Fourth, the inclusion of electrophysiological measures (EEG-derived P300) provides an important mechanistic dimension, enabling the assessment of neurophysiological changes associated with aTBS and offering potential biomarkers of treatment response. Collectively, these methodological features strengthen both the clinical relevance and mechanistic interpretability of the trial.

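### The intervention section implies 20 stimulation sessions per participant while three other places give 10, so the stated cumulative dose differs twofold

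*Protocol article*

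**What the plan says.** Four places in the protocol article describe the amount of stimulation.

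- **Abstract, Methods and analysis:** "10 weekday sessions; 3600 pulses per session".
- **Study design:** "3,600 pulses per session, 10 sessions total". Weekdays are not mentioned here.
- **Discussion, among the strengths:** "10 sessions across 10 weekdays". No pulse count is given here.
- **aTBS protocol (the intervention section):** "Participants in the active group receive sequential bilateral aTBS twice daily for 10 treatment days", followed by "The interval between the two daily treatment sessions in this study is set at 3 hours" and three reasons for that gap (safety, neurophysiological recovery, tolerability).

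The aTBS protocol section also describes what one application contains: "cTBS applied to the right DLPFC followed immediately by iTBS applied to the left DLPFC", with 1,800 pulses in each part. It says that the iTBS part consists of three 600-pulse trains of 3 min 9 s with 10-second gaps, and gives its total length as 570 s.

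**The concern.** The abstract, Study design and Discussion all give 10 sessions. Spread over 10 weekdays, as in the abstract and Discussion, that is one a day. The intervention section gives two a day for 10 days. These cannot all be true, and the difference is in the amount of the experimental treatment.

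At stake is the identity of the tested regimen. A reader who wants to replicate the trial, pool it with others or compare its dose with another protocol needs one cumulative figure. The Introduction makes such a comparison itself: it puts SAINT at 90,000 pulses in total and says that sequential aTBS is meant to lower the overall treatment burden relative to it. How much lower depends on which schedule is meant. The Discussion presents a schedule of one session a day as a strength, whereas the intervention section justifies a within-day gap that has no purpose under that schedule.

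**Working it through.** **Pulses per session.** The inputs are from the aTBS protocol section: 1,800 (right cTBS) + 1,800 (left iTBS) = 3,600. This reproduces the per-session figure in the abstract and in Study design, so the content of one session agrees across the document.

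**Total sessions.** Sessions = sessions per day × treatment days. From the aTBS protocol section this is 2 × 10 = 20. The stated total in Study design is 10, so that figure is not reproduced.

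**Cumulative pulses per participant.** Pulses = sessions × 3,600.

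| Source | Sessions | Pulses per session | Cumulative pulses |
|---|---|---|---|
| Abstract | 10 | 3,600 (stated) | 36,000 |
| Study design | 10 | 3,600 (stated) | 36,000 |
| Discussion | 10 | not stated; 3,600 taken from the two rows above | 36,000 |
| aTBS protocol | 2 × 10 = 20 | 1,800 + 1,800 = 3,600 | 72,000 |

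The ratio is 72,000 / 36,000 = 2. Against the 90,000 pulses that the Introduction gives for SAINT, the totals are 36,000 / 90,000 = 40% and 72,000 / 90,000 = 80%.

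**Can a kinder reading reconcile the text?** Three were tried.

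1. *A session means a treatment day.* One day would then hold 2 × 3,600 = 7,200 pulses, against the 3,600 per session stated in the abstract and Study design. The intervention section also uses the word session for each of the two daily applications.
2. *The two daily sessions are the cTBS part and the iTBS part, given separately.* The section excludes this, because iTBS follows cTBS immediately within one application, while the two sessions are 3 hours apart.
3. *Twice daily for 5 days, which would give 10 sessions.* This contradicts both the 10 treatment days of the intervention section and the 10 weekdays of the Discussion.

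None of them works.

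**iTBS timing (side note).** Each train lasts 3 min 9 s = 189 s. Three trains with two 10-second gaps last 3 × 189 + 2 × 10 = 567 + 20 = 587 s. The stated length is 570 s, a difference of 17 s (about 3%). The count of 3 × 600 = 1,800 pulses is not affected.

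**The case against.** The strongest reply is that the intervention section is the operative text. It is specific, and its three-part rationale for the 3-hour gap makes the twice-daily wording unlikely to be a stray slip. The other three places are an abstract, an overview and a discussion, and staff would not normally treat patients from those. Figure 2, whose caption covers timing and parameters, is not shown and may set out the schedule plainly.

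Part of this stands. It is a fair reason not to assume that treatment would be delivered inconsistently. It does not settle which schedule is meant: the total of 10 in Study design is explicit and two other places support it. Whatever Figure 2 contains, at least one set of statements in the text would still be wrong.

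A reader might also infer more than the document supports:

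- **That the exposure is undefined.** This is too strong. The content of a session is consistent, and the 10 treatment days agree across the abstract, the intervention section, the Discussion and the Day 1 to Day 10 schedule in Table 1. Only sessions per day, and the totals that follow from it, conflict.
- **That operators would give different doses to different participants.** Nothing in the document shows this.
- **That the active-sham comparison is biased.** The sham arm is to have the same targets, treatment duration and procedures, so whichever schedule is run is meant to apply to both arms. The definition of the primary endpoint is not touched.
- **That adherence and adverse-event rates lose their denominator.** The article specifies no adherence measure and no per-session rate. It says only that events are recorded at each session and follow-up visit. Such definitions may sit in a fuller document.
- **That the registry entry disagrees.** That record is not available here, so no mismatch with it can be claimed.

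**Conclusion.** The contradiction holds. The current text gives both 10 and 20 sessions, hence both 36,000 and 72,000 pulses per participant, a factor of 2. No visible passage reconciles them. The finding rests on the stated 3,600 pulses per session, which the section's own components reproduce, and on reading session as the intervention section uses it. For the Discussion, the pulse total assumes the per-session figure given elsewhere.

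The consequence is limited but important: the regimen to which any result would be attributed is not fixed. This is an internal inconsistency in the dose, not a bias in the treatment comparison. The documents do not settle which schedule is intended, and no view is taken on it here. The 17-second timing discrepancy is minor, and the conclusion does not depend on it.

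**What to change.** The investigators should reconcile the abstract, Study design, aTBS protocol and Discussion to one stated number of sessions per day, one total number of sessions and one total number of pulses per participant, and check Figure 2 against the result. Which regimen applies is for them to state. The word session should have one meaning throughout, so that the total follows by multiplication.

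In the same correction, the train length, gap length and total iTBS duration should be reconciled so that they add up.

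The cost is a wording correction. An amendment would be needed only if the approved regimen differs from the reconciled text. Sample size, endpoints and analysis are unaffected.

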**Figure 2 f2:**
[figure not shown]
Timing and parameters of sequential aTBS intervention.

All participants will continue to receive standardized routine clinical care—including daily psychotherapy-based skills training—administered according to a fixed protocol that will be independent of treatment allocation. If patients’ symptoms persist following these interventions, the therapist will refer them to a specialist. Detailed parameters and equipment specifications are provided in **Figure 2**; **Table 3**.

### Study outcomes

#### Primary outcome

The primary outcome is to compare the response rate of depressive symptoms between the active stimulation group and the sham stimulation group after intervention. The response rate is defined as a reduction of 50% or more in the HAMD-17 score compared with the baseline. Remission is defined as a HAMD-17 score of ≤ 7 (32).

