### Objectives

The primary objective of this randomized controlled trial is to evaluate the clinical efficacy of sequential accelerated Theta Burst Stimulation (aTBS) in adults with MDD. Our central hypothesis is that, compared to sham stimulation, sequential aTBS will induce a faster and more significant alleviation of depressive symptoms, with this therapeutic effect remaining significant throughout the subsequent 2-week and 4-week follow-up periods. A secondary objective of this study is to systematically evaluate the safety, tolerability, and adverse event profile of sequential aTBS in the target population. For this safety assessment, the Treatment Emergent Symptom Scale (TESS) will be administered to capture and characterize common adverse events, including headache, dizziness, nausea, scalp discomfort, and muscle twitching. For mechanistic exploration, this study will employ high-temporal-resolution EEG to capture the P300 event-related potential as a neurophysiological indicator, aiming to elucidate the mechanisms by which aTBS modulates cortical excitability and cognitive-emotional processing, thereby identifying potential biomarkers for future treatment strategies.

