### Statistical analysis

#### Sample size

The sample size for this exploratory trial was determined *a priori* using G*Power software (version 3.1). An F-test was employed based on an effect size (Cohen’s d) of 0.38 by Chu et al. (2021). A total of 50 participants were required to achieve 80% statistical power at a two-sided alpha level of 0.05 (37). Anticipating an approximate dropout rate of 10%, the planned enrollment was at 56 participants.

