#### Analysis of clinical data

All statistical analyses will be conducted using SPSS version 26.0. Continuous variables will be presented as means ± standard deviations or medians (interquartile ranges), depending on distribution, and compared using independent samples t-tests or Mann-Whitney U tests, as appropriate. Categorical variables will be expressed as frequencies (%) and analyzed using Chi-square or Fisher’s exact tests. A repeated-measures analysis of variance (ANOVA) will be applied to evaluate longitudinal changes in each outcome, with group (active vs sham) as the between-subject factor and time (baseline, post-intervention, follow-up) as the within-subject factor. If the assumption of sphericity is violated according to Mauchly’s test, the Greenhouse-Geisser correction will be applied. Significant interactions will be followed by Bonferroni-adjusted simple-effects comparisons to determine between-group differences at each time point and within-group changes across time.

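### The primary test dichotomises HAMD-17, although the hypothesis and the sizing method are about degree of change; at the stated d = 0.38 this costs the primary comparison about 4 to 12 points of power

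*Protocol article*

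**What the plan says.** - The Primary outcome section (under Study outcomes) reads: "The primary outcome is to compare the response rate of depressive symptoms between the active stimulation group and the sham stimulation group after intervention". Then: "The response rate is defined as a reduction of 50% or more in the HAMD-17 score compared with the baseline". Remission is defined there as a score of 7 or less. The abstract names both response and remission rates as primary.
- Objectives: the central hypothesis is that, against sham, "sequential aTBS will induce a faster and more significant alleviation of depressive symptoms".
- Sample size: "An F-test was employed based on an effect size (Cohen’s d) of 0.38", and "A total of 50 participants were required to achieve 80% statistical power at a two-sided alpha level of 0.05". The endpoint behind the effect size is not named, and no response rate is assumed for either arm.
- Analysis of clinical data: "Categorical variables will be expressed as frequencies (%) and analyzed using Chi-square or" Fisher's exact test. The same section plans a repeated-measures ANOVA, group by time, on each outcome.
- Study design and Table 1: HAMD-17 is rated at baseline (T0), after the last session (T1), and at the 2-week and 4-week follow-ups.

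**The concern.** The hypothesis is a matter of degree, and an F-test with Cohen's d is a method for means. The primary outcome is a proportion. Cutting the score at a 50% fall counts a 49% improvement as failure and treats 50% and 90% improvements as equal. The discarded information has been collected anyway: every patient has a HAMD-17 total at T0 and T1.

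With 25 to 28 patients per arm there is little power to spare. At stake is the headline conclusion: the primary test could be null while the same T1 ratings, analysed as a score, show a difference. The article cites a source for the definitions of response and remission but gives no reason for preferring the cut to the score as the primary analysis.

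**Working it through.** **Inputs from the article.** 56 randomised 1:1; 50 evaluable, so 25 per arm; two-sided alpha 0.05; d = 0.38; chi-square or Fisher for categorical outcomes.

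**Assumptions, not in the article.** Sham response 10–40%; normally distributed scores; correlation of 0.4–0.5 between baseline and T1 HAMD-17.

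**The plan's own figure.** A two-group comparison of means at d = 0.38 needs n = 2(1.960 + 0.842)² / 0.38² = 108.7, so 109 per arm (218 in total), not 50. If 0.38 is read as Cohen's f, then d = 2f = 0.76 for two equal groups; a one-way F-test needs 58 and has 75% power at 50. A total near 50 appears only with repeated-measures inputs that the article does not state (for example f = 0.19, three measures and correlation 0.5 give 48). The dropout step is right: 50 / 0.9 = 55.6, so 56. Because the reading is uncertain, both d = 0.38 and d = 0.76 are carried below.

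**Power on the score.** Noncentrality is d√(n/2). With n = 25 and 48 degrees of freedom:
- d = 0.38: 0.38 × 3.536 = 1.34, power 26.1%
- d = 0.76: 0.76 × 3.536 = 2.69, power 75.0%

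Baseline adjustment replaces d by d/√(1 − r²), with one degree of freedom fewer:
- d = 0.38: becomes 0.415 (r = 0.4) or 0.439 (r = 0.5), power 30.0% or 33.0%
- d = 0.76: power 81.9% or 86.0%

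**Power on response.** The same shift on the normal scale gives an active rate p₁ = Φ(Φ⁻¹(p₀) + d). Power is by exact binomial enumeration, 25 per arm, uncorrected chi-square:

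| d | Sham p₀ | Active p₁ | Chi-square | Fisher | t-test on score | t-test gain over chi-square (points) |
|---|---|---|---|---|---|---|
| 0.38 | 10% | 18.4% | 14.0% | 6.3% | 26.1% | 12.0 |
| 0.38 | 20% | 32.2% | 17.2% | 9.3% | 26.1% | 8.8 |
| 0.38 | 30% | 44.3% | 19.8% | 12.3% | 26.1% | 6.3 |
| 0.38 | 40% | 55.0% | 21.9% | 14.2% | 26.1% | 4.2 |
| 0.76 | 10% | 30.1% | 45.3% | 30.8% | 75.0% | 29.6 |
| 0.76 | 20% | 46.7% | 54.5% | 41.2% | 75.0% | 20.5 |
| 0.76 | 30% | 59.3% | 60.3% | 48.5% | 75.0% | 14.7 |
| 0.76 | 40% | 69.4% | 60.4% | 48.7% | 75.0% | 14.5 |

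The smallest gain (4.2) is flattered by the chi-square test, whose true size at 25 per arm and a 40% rate is about 6.0%. At 28 per arm and d = 0.38 the gain is 9.1 to 13.9 points.

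**Check with the actual 50% rule.** A simulation (baseline mean 23, SD 4, floored at 17; T1 SD 6; correlation parameter 0.4; 25 per arm; sham response about 11%, 21% and 34%) gave:
- d = 0.38: chi-square 16.2–24.1%, t-test about 26%, ANCOVA 29.5–29.8%
- d = 0.76: chi-square 54.0–67.7%, t-test about 75%, ANCOVA about 81%

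Percentage response already uses the baseline, so the unadjusted t-test gains less here (about 2 to 10 points at d = 0.38, 7 to 21 at d = 0.76). ANCOVA gains about 5.5 to 13 and 13 to 27 points. The score is ahead in every case.

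**The case against.** **The score is already in the plan.** Repeated-measures ANOVA is planned on each outcome, with between-group comparisons at each time point after a significant interaction. This stands. The T1 score will very probably be analysed and reported, so a reader should not infer that the trial as a whole loses this power, or that a null response result would be the only efficacy evidence. What remains is that the score is not the primary outcome.

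**The sizing may not concern HAMD-17.** This stands too. The Sample size section names no endpoint. That the sizing is about the HAMD-17 score is a natural reading of an F-test and Cohen's d, but it is an inference. What the text does show is that no response rates were used.

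**The large losses rest on outside inputs.** A loss near 30 points needs both d of about 0.76 and a sham response of 10%, and the article states neither. At the stated d = 0.38 the t-test gain is 4 to 12 points on a power of only 26%, so changing the scale does not by itself make the trial adequately powered.

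**Response is a conventional endpoint.** It is defined with a citation, it allows comparison with the conventional-TMS rates in the Introduction (29–46% response, 18–32% remission), and the trial calls itself exploratory. That is a good reason to report response, but not to put the main test on the less sensitive scale. Nor does a response outcome contradict the hypothesis; it measures it more coarsely.

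**Conclusion.** The point holds as an inexpensive improvement to the primary analysis; the article does not misstate anything here. At 25 per arm and the stated d = 0.38, the primary chi-square test has about 14–22% power, against 26% for the uncut score and 30–33% with baseline adjustment. With 0.38 read as Cohen's f, it has 45–60%, against 75% and 82–86%. The size of the gap depends on the assumed sham response, normality and baseline correlation; its direction was the same in every case examined. The loss is confined to the primary comparison and the headline drawn from it. A reader might infer a general loss of about 30 points, or that the trial cannot show an effect on the score. The article supports neither: the first is one corner of an assumed grid, and the second overlooks the planned ANOVA.

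**What to change.** - In the abstract and under Primary outcome, name the HAMD-17 total score at T1 as the single primary outcome, compared between arms by ANCOVA with baseline HAMD-17 as covariate and reported as an adjusted mean difference with 95% CI.
- Keep response (50% or greater reduction) and remission (7 or less) as secondary outcomes, each as a risk difference with 95% CI.
- Base the Sample size statement on that score comparison, naming the endpoint, the effect measure and the assumed baseline correlation. For orientation, 25 per arm gives 80% power at d of about 0.81 unadjusted, or about 0.70–0.74 with adjustment (0.81 × √(1 − r²), r = 0.5 to 0.4).

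If the investigators prefer to keep response as primary, the sizing should state response rates. For sham rates of 10–40%, 80% power needs roughly 172–272 per arm at d = 0.38 or 44–62 at d = 0.76.

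**Cost.** No new visits, ratings or patients. The real cost is changing a registered primary outcome in a trial scheduled from September 2025, in which the staff who treat and rate know the allocation; this could look like outcome switching. The headline also becomes less directly comparable with published response rates. Make a dated protocol and registry amendment before anyone looks at outcome data by arm, state the reason, and still report the originally registered response comparison in full.
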